##### Low transmission strata

Based on the number of clusters available in the low transmission strata (n = 10 in each of the three treatment groups, total of 30 clusters), the observed CV (CV = 0.41), a statistical power of 80 %, a probability of committing a type two error of 5 % (one-tailed test), and simple random sampling used to obtain the sample of children in each household survey, a sample size of 39 children under six-years-old per HFCA per treatment group will be needed to detect 6 % absolute detectable difference in parasite prevalence between any two groups from a baseline of 10 % (a 60 % relative difference going from 10 to 4 % parasite prevalence). This detectable difference equates to a crude odds ratio of 0.38. With survey non-response assumed to 20 %, a sample size of 470 children per treatment group (47 children per cluster), totaling 1,410 children under six-years-old per survey round will be sought (Additional file 1: Table S2). This sample size equates to a sample size of 1,410 households sampled per survey round.

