**Methods/design:**

The study will be conducted along Lake Kariba in Southern Province, Zambia; an area of low to moderate malaria transmission and high coverage of vector control. A community randomized controlled trial (CRCT) of 60 health facility catchment areas (HFCAs) will be used to evaluate the impact of two rounds of MDA and fMDA interventions, relative to a control of no mass treatment, stratified by high and low transmission. Community residents in MDA HFCAs will be treated with DHAp at the end of the dry season (round one: November to December 2014) and the beginning of the rainy season (round two: February to March 2015). Community residents in fMDA HFCAs will be tested during the same two rounds for malaria parasites with a rapid diagnostic test; all positive individuals and all individuals living in their household will be treated with DHAp. Primary outcomes include malaria parasite prevalence (n = 5,640 children aged one month to under five-years-old), as measured by pre- and post-surveys, and malaria parasite infection incidence (n = 2,250 person-years among individuals aged three months and older), as measured by a monthly longitudinal cohort. The study is powered to detect approximately a 50 % relative reduction in these outcomes between each intervention group versus the control.

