**Fig. 1 Fig1:**
[figure not shown]
Map of the study area, divided into 60 health facility catchment areas that serve as the unit of randomization

The area is primarily composed of the Tonga ethnic group. Livelihood typically consists of fishing and farming. While there are towns in the study area, the majority of the area is rural. The health system throughout the study area consists primarily of public sector health facilities, with health facility catchment areas (HFCAs) typically covering 500 to 1,500 households. All HFCAs were mapped and geographically defined prior to this study.

Malaria transmission in this area is low to moderate, with malaria parasite prevalence ranging from less than 1 % in some areas to more than 25 % in other areas. The high malaria transmission season in the study area follows the rainy season and lasts from January to May. Results from the 2012 MTAT-AL intervention identified two distinct areas of malaria transmission intensity, with higher transmission areas along the low-lying shores of Lake Kariba, and lower transmission areas inland from Lake Kariba.

There are current efforts to maintain high vector control coverage in the study area, with household coverage of LLINs estimated to be between 60 and 80 %. Additionally, a comprehensive IRS campaign to cover all households in the study area was conducted between November 2014 and January 2015, using the highly effective insecticide Actellic.

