#### Stratification

As the impact of the MDA and fMDA interventions are expected to vary across malaria transmission strata, the 60 HFCAs included in the study have been stratified into high and low transmission strata. To do this, parasite prevalence in each HFCA was estimated with a kriged continuous surface of parasite prevalence from data from the baseline 2014 parasite survey. Catchments were then ranked from highest to lowest parasite prevalence. The top 30 HFCAs were included in the high transmission strata, while the bottom 30 were included in the low transmission strata; the resulting cut point between the high and low transmission strata was approximately 10 % parasite infection prevalence.

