Noted weaknesses of this trial include a less than ideal number of community randomization units (N = 60), especially when stratified by high (n = 30) and low (n = 30) transmission strata. The sample size within the high and low transmission strata will only allow the detection of approximately a 50 % reduction in parasite prevalence and infection incidence between intervention groups, with 80 % statistical power; the threat of a type two error is therefore higher than ideal. The primary analysis will be based on the intention-to-treat principle; there is potential for misclassification of exposure using this approach. Secondary analysis using a per-protocol approach will be used mitigate any misclassification of exposure. And lastly, there is always the potential for error in the measurement of outcomes, exposure to the interventions, and potential confounding factors in such a large and complex trial. We have gone to considerable length to try and minimize such error through the use of electronic data capture systems in the field and robust diagnostic methods.

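### Low-transmission stratum: prevalence power is computed at a 10 % control mean, which is the stratum's upper edge, and the claim of about a 50 % detectable reduction conflicts with the plan's own 60 %

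*Protocol article*

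**What the plan says.** - **Sample size, household parasite surveys, Low transmission strata.** The detectable difference is stated "in parasite prevalence between any two groups from a baseline of 10" %, described as "a 60 % relative difference going from 10 to 4 % parasite prevalence". The inputs are 39 children per HFCA, "n = 10 in each of the three treatment groups, total of 30 clusters", "the observed CV (CV = 0.41"), 80 % power and a one-tailed 5 % level. The 39 children become 47 to allow for 20 % non-response.
- **Stratification.** The 60 HFCAs were ranked on a kriged prevalence surface built from the 2014 baseline survey. The lower 30 form the low stratum, and "the resulting cut point between the high and low transmission strata was approximately 10 % parasite infection prevalence".
- **Study site.** The area is described "with malaria parasite prevalence ranging from less than 1 % in some areas to more than 25 % in other areas".
- **Abstract, Methods/design.** "The study is powered to detect approximately a 50 % relative reduction in these outcomes". The abstract's discussion paragraph places this limit within the high and low strata.
- **Discussion.** Power of 80 % within each stratum is listed as a strength. Among the weaknesses, the within-stratum sample size "will only allow the detection of approximately a 50 % reduction in parasite prevalence and infection incidence", again with 80 % power.
- **Sample size, RDT positivity.** The low-stratum calculation for this primary outcome uses the same 10 % baseline and CV of 0.41.

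**The concern.** Two statements about the low stratum do not fit together. If the stratum holds the 30 HFCAs that fall below about 10 %, its mean cannot also be about 10 % unless nearly all of them sit at the boundary. The CV assumed for the stratum speaks against that. With a mean of 10 % and a CV of 0.41 the between-HFCA standard deviation is 4.1 points, so one standard deviation above the mean is 14.1 %, well past the boundary that defines the stratum. The Study site section also puts some areas below 1 %.

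A second conflict needs no view on the true mean. The summary claim of about a 50 % detectable reduction within strata is more favourable than the 60 % that the plan itself derives for low-stratum prevalence.

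At stake is how a null low-stratum result is read. A reader relying on the abstract or Discussion would take it as evidence against a halving of prevalence, an effect that the stated design had well under 80 % power to detect.

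**Working it through.** **Inputs**, all from the low-stratum survey sample size section: c = 10 HFCAs per arm, m = 39 children per HFCA, k = 0.41, p0 = 0.10, p1 = 0.04, power 80 %, one-sided 5 %. The text calls the 5 % a type two error; I read it as the one-sided significance level, because only that reproduces the stated sample size.

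**Formula** (Hayes and Moulton, unmatched proportions, the method the plan names):

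V = p0(1−p0)/m + p1(1−p1)/m + k²(p0² + p1²)

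c = 1 + (1.645 + 0.842)² × V / (p0 − p1)²

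power = Φ( √[(c − 1)(p0 − p1)² / V] − 1.645 )

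**Step 1: reproduce the plan (10 % to 4 %).**
V = 0.00231 + 0.00098 + 0.00195 = 0.00524.
c = 1 + 6.183 × 0.00524 / 0.0036 = 10.0.
power = Φ(√(9 × 0.0036 / 0.00524) − 1.645) = Φ(2.486 − 1.645) = 80.0 %.
Solving for m returns 39.0. The arithmetic is right on its inputs.

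**Step 2: a 50 % reduction on the plan's own inputs (10 % to 5 %).**
V = 0.00231 + 0.00122 + 0.00210 = 0.00563.
power = Φ(√(9 × 0.0025 / 0.00563) − 1.645) = Φ(2.000 − 1.645) = 64 %.
Reaching 80 % would take about 89 children per HFCA. With all 47 sampled children, power is 68 %.

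**Step 3: means below the cut point.** The documents do not give the low-stratum mean, so these means are assumptions. CV is held at 0.41.

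| Assumed control mean | Power, 60 % reduction, m = 39 | Same, m = 47 | Reduction detectable with 80 % power, m = 39 | Power, 50 % reduction, m = 39 |
|---|---|---|---|---|
| 10 % (plan) | 80 % | 84 % | 60 % | 64 % |
| 9 % | 77 % | 82 % | 62 % | 61 % |
| 7 % | 71 % | 75 % | 67 % | 55 % |
| 5 % | 61 % | 66 % | 74 % | 46 % |

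Worked example at 7 % (7 % to 2.8 %, m = 39): V = 0.00167 + 0.00070 + 0.00096 = 0.00332 (summed before rounding); power = Φ(√(9 × 0.042² / 0.00332) − 1.645) = Φ(2.186 − 1.645) = 71 %.

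**Step 4: set the summary claim beside its sources.** The stratum-specific detectable reductions in the sample size sections are 40 % (high-stratum prevalence), 60 % (low-stratum prevalence), 49 % (high-stratum incidence) and 53 % (low-stratum incidence). About 50 % describes the two incidence figures and is conservative for high-stratum prevalence. It is not met for low-stratum prevalence.

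**The case against.** The strongest reply is that the calculation is correct and only a planning value is in question. The 47-household sample was already drawn for the 2014 survey, while the cut point came out of that survey, so the 10 % appears to be an earlier assumption that was never updated. That is a fair account of how the mismatch may have arisen, but the article prints both figures as current.

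Several further points stand and limit the finding:

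- The cut point is approximate, comes from a kriged surface, and its diagnostic is not stated. Outcome one uses both RDT and PCR, and the Background says RDTs can miss up to half of low-density infections. If the surface rests on RDT, PCR prevalence would be higher.
- The 39 children per HFCA may be too few. The survey takes all children under six in 47 households. With 60 children per HFCA, an illustrative figure, power for a 60 % reduction at a 7 % mean would be 81 %, ignoring correlation within households.
- The pre/post model might recover some power, though the stated calculation does not use it.
- The Discussion already admits that the type two error risk is higher than ideal. It does so using the 50 % figure, so it understates the low-stratum gap.

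A reader might also infer that the 30 % high-stratum baseline is impossible. The documents do not support that: the upper figure for the area is open-ended (more than 25 %) and gives no age group, season or diagnostic. With CV 0.31 and m = 39, a 50 % reduction there has 94 % power at a 30 % mean, 88 % at 20 % and 82 % at 15 %. Nor can a loss be put on the indoor spraying campaign before the 2015 survey, because no effect size is given.

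**Conclusion.** The point holds for the low stratum only, in two parts.

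First, the 10 % control mean conflicts with a stratum defined as lying below about 10 %. The stated 80 % power for a 60 % reduction therefore rests on an input that the stratification contradicts, on the measure used for stratifying. The size of the loss is uncertain. With 39 children per HFCA, power is 77 % to 61 % for assumed means of 9 % to 5 %. If all 47 respond it is 82 % to 66 %, so a mean near 9 % with full response leaves no shortfall against 80 %. These figures assume CV 0.41, one child per sampled household and no gain from baseline adjustment.

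Second, and independent of the true mean, the claim of about a 50 % detectable reduction in prevalence within strata at 80 % power contradicts the plan's own 60 % for the low stratum. On the plan's inputs, power for 50 % is 64 %.

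It would go too far to say that the low-stratum mean is known to be 5 % or less, or that the trial as a whole is underpowered. The mean is not reported, and the other three stratum-specific figures are 40 %, 49 % and 53 %. For RDT positivity the same 10 % is reused, but in people of three months and older, so the children's cut point bears on it only indirectly.

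**What to change.** - Recompute the low-stratum detectable reduction from the observed 2014 baseline mean and CV, using the diagnostic that defines the outcome and the number of children actually obtained per HFCA. If RDT and PCR are both kept, give both.
- Restate the Low transmission strata section accordingly. State which diagnostic underlies the cut point, so that it and the baseline can be compared.
- Revisit the 10 % baseline and CV in the low-stratum RDT positivity calculation, using the age range of that outcome.
- In the abstract and the Discussion, replace the single figure of about 50 % with the figures for each stratum and outcome. Unless the recalculation changes it, low-stratum prevalence should read 60 %.

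The 2014 survey is complete and was already used to form the strata, so the inputs exist. The cost is a short recalculation and a less favourable low-stratum statement. The number of HFCAs, the number of children, the randomization and the analysis do not change.

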#### Longitudinal cohort

##### High transmission strata

The CV for infection incidence was based on estimates of OPD confirmed case incidence for HFCAs for 2012 (CV = 0.50). Based on the 30 HFCAs available in the high transmission strata, a statistical power of 80 %, a probability of committing a type two error of 5 % (one-tailed test), a sample size of 25 individuals aged three-months-old and older per HFCA (cluster) per treatment group will be needed to detect an absolute detectable difference in 12-month cumulative parasite infection incidence between any two groups from an assumed baseline of 1.8 infections per person per year to 0.91 infections per person per year (a 49 % relative reduction). With a loss to follow-up rate assumed to be 33 %, a sample size of 375 individuals per treatment group (38 per HFCA) will be enrolled and followed up on monthly, totaling 1,125 individuals aged three-months-old and older enrolled in the cohort study in the high transmission strata (Additional file 1: Table S3).

##### Low transmission strata

The CV for infection incidence was based on estimates of OPD confirmed case incidence for HFCAs in 2012 (CV = 0.50). Based on the 30 HFCAs available in the low transmission strata, a statistical power of 80 %, a probability of committing a type two error of 5 % (one-tailed test), a sample size of 27 individuals aged three-months-old and older per HFCA (cluster) per treatment group will be needed to detect absolute detectable difference in parasite infection incidence between any two groups from an assumed baseline of 0.6 infections per person per year to 0.28 infections per person per year (a 53 % relative reduction). With a loss to follow-up rate assumed to be approximately 33 %, a sample size of 375 individuals per treatment group (38 per cluster) will be enrolled and followed up on monthly, totaling 1,125 individuals enrolled in the cohort study in the low transmission strata (Additional file 1: Table S3).

#### Rapid diagnostic test positivity during campaign rounds

It is estimated based on the population sizes of the MDA and fMDA HFCAs, a sample size exceeding 50,000 individuals aged three-months-old and older in each group (approximately 5,000 per HFCA) will be achieved. As described above, a sample size of 750 individuals aged three-months-old and older in the cohort in the control HFCAs will provide contemporaneous measure of RDT positivity in areas without intervention rounds (n = 375 individuals in the high transmission strata and 375 individuals in the low transmission strata). This sample size in areas of high transmission will provide 80 % statistical power to detect a 33 % difference (an absolute decrease from 30 to 20 %; odds ratio of 0.58) in RDT positivity between the control group and either of the MDA groups, assuming a baseline prevalence of 30 %, a CV = 0.31, 10 HFCAs in each treatment group, and a probability of committing a type two error of 5 % (one-tailed test). This sample size in areas of low transmission will provide 80 % statistical power to detect a 50 % difference (an absolute decrease from 10 to 5 %; odds ratio of 0.47) in RDT positivity between the control group and either of the MDA groups, assuming a baseline prevalence of 10 %, a CV = 0.41, 10 HFCAs in each treatment group, and a probability of committing a type two error of 5 % (one-tailed test).

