#### Sample size and statistical power

The maximum number of cluster units available was 60, split evenly with 10 clusters per MDA, fMDA, and control groups in the high and low transmission strata. Sample size was derived using a formula for CRCTs developed by Hayes and Moulton [16]. Sample sizes are estimated to assess statistical differences comparing the four primary outcomes for the MDA group against no intervention (control), and for the fMDA group against no intervention (control).

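### The stated 80% power for RDT positivity does not follow from its own inputs, which give about 72% in both strata

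*Protocol article*

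**What the plan says.** The section on sample size and statistical power gives one method for all four primary outcomes: "Sample size was derived using a formula for CRCTs developed by Hayes and Moulton". It also fixes the clusters: "The maximum number of cluster units available was 60, split evenly with 10 clusters per MDA, fMDA, and control groups in the high and low" (that is, within each of the two strata).

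The subsection on RDT positivity during campaign rounds then gives its own inputs. In the intervention arms, "a sample size exceeding 50,000 individuals aged three-months-old and older in each group (approximately 5,000 per HFCA) will be achieved". Controls come from the longitudinal cohort: "n = 375 individuals in the high transmission strata and 375 individuals in the low transmission strata". The CVs are 0.31 (high) and 0.41 (low), with 10 HFCAs per arm and a one-tailed 5% test.

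On these inputs it claims, for the high stratum, "This sample size in areas of high transmission will provide 80 % statistical power to detect a 33 % difference", spelled out as "an absolute decrease from 30 to 20 %; odds ratio of 0.58". For the low stratum it claims "This sample size in areas of low transmission will provide 80 % statistical power to detect a 50 % difference", spelled out as 10% to 5% with an odds ratio of 0.47.

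The 375 is an enrolment figure. The cohort sample size for the high stratum reads: "With a loss to follow-up rate assumed to be 33 %, a sample size of 375 individuals per treatment group (38 per HFCA"). The low stratum uses the same number.

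**The concern.** The survey calculation in the same article needs 39 children per HFCA in both arms to detect 30% to 18% with 80% power, at the same CV of 0.31 and the same number of clusters. For RDT positivity the target is a smaller difference (30% to 20%), and the control arm has slightly fewer people per HFCA (37.5). The only gain is the very large intervention sample. That sample removes the within-cluster sampling error of one arm, but it touches neither the between-HFCA variance nor the control arm's sampling error. It is doubtful that this can pay for the smaller difference.

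RDT positivity is listed as a primary outcome, and the Discussion names 80% power within each stratum as a strength of the trial. If the figure is too high, a null result on this outcome would be read with more confidence than the design supports.

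**Working it through.** **Formula.** Unmatched Hayes and Moulton formula, solved for power, with c clusters per arm, m people per cluster and between-cluster CV k:

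power = Φ( √[ (c − 1)(p0 − p1)² / V ] − 1.645 ), where V = p0(1 − p0)/m0 + p1(1 − p1)/m1 + k²(p0² + p1²).

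For rates, the first two terms of V become (r0 + r1)/y, with y person-years per cluster. The value 1.645 is the one-tailed 5% point. The article calls the 5% a type two error. It is read here as the type one error, because power is given separately as 80%.

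**Step 1: reproduce the plan's other figures (c = 10, so c − 1 = 9).**

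- Survey, high, 30% to 18%, m = 39, k = 0.31: V = 0.00538 + 0.00378 + 0.01176 = 0.02093; 9 × 0.0144/0.02093 = 6.19; √6.19 − 1.645 = 0.843; power 80.1%.
- Survey, low, 10% to 4%, m = 39, k = 0.41: V = 0.00231 + 0.00098 + 0.00195 = 0.00524; 9 × 0.0036/0.00524 = 6.18; power 80.0%.
- Cohort, high, 1.8 to 0.91, y = 25, k = 0.50: power 80.8%.
- Cohort, low, 0.6 to 0.28, y = 27, k = 0.50: power 81.6%.

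All four agree with the stated 80% to within 2 points, and the survey figures almost exactly. So the formula, the c − 1 form and the one-tailed 5% appear to be what the authors used.

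**Step 2: RDT positivity with its stated inputs (m0 = 375/10 = 37.5, m1 = 5,000).**

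- High, 30% to 20%, k = 0.31: V = 0.21/37.5 + 0.16/5,000 + 0.0961 × (0.09 + 0.04) = 0.00560 + 0.00003 + 0.01249 = 0.01813; 9 × 0.01/0.01813 = 4.966; √4.966 − 1.645 = 0.583; power **72.0%**.
- Low, 10% to 5%, k = 0.41: V = 0.09/37.5 + 0.0475/5,000 + 0.1681 × (0.01 + 0.0025) = 0.00240 + 0.00001 + 0.00210 = 0.00451; 9 × 0.0025/0.00451 = 4.988; √4.988 − 1.645 = 0.589; power **72.2%**.

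**Step 3: how far the conventions matter.**

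| Variant | High | Low |
|---|---|---|
| As stated | 72.0% | 72.2% |
| 38 controls per HFCA | 72.2% | 72.5% |
| 2,500 per intervention HFCA (50,000 over both strata) | 72.0% | 72.1% |
| t-based, 18 df | 73.0% | 73.2% |
| c in place of c − 1 | 75.9% | 76.1% |

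**Step 4: what would give 80%.** Keeping c − 1 and 37.5 controls per HFCA, the detectable alternatives are 30% to 19.0% (37% relative, odds ratio about 0.55) and 10% to 4.5% (55% relative, odds ratio about 0.42). The effects as stated would need about 12.2 HFCAs per arm, against the 10 available.

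**Step 5: round two.** Round one coincides with cohort enrolment, so 375 applies there. Round two runs from February to mid-March 2015, about three to four months later. The article gives no loss figure for that point. If the 33% twelve-month loss accrued linearly (an assumption), 8% to 11% would be gone (33% × 3/12 to 33% × 4/12), leaving 33.4 to 34.4 controls per HFCA. Power would then be about 71% (high) and 70% (low).

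**The case against.** Four points can be made for the plan.

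- **The variant of the formula is not named.** Without the extra cluster, power is about 76%, and 80% is reached at about 19.5% and 4.7%, which could have been rounded to 20% and 5%. This stands only in that the size of the gap depends on the convention. The survey figures fit c − 1, and the printed odds ratios, 0.58 and 0.47, are those of exactly 20% and 5%, unless they were computed after rounding.
- **Controls might be tested twice within a round**, since visits are every four weeks and a round spans more than a month. At 75 independent tests per HFCA the formula gives 78.2% and 83.2%. But repeat tests on one person are correlated, and the article counts individuals, 375 per stratum. This is an upper bound, and it still misses 80% in the high stratum.
- **The consequence is modest.** The detectable value moves by 1.0 percentage point (high) and about 0.5 (low). The number of clusters was the maximum available, and the control sample is a by-product of the cohort. The Discussion already concedes limited power. All of this stands, and it makes the point a correction rather than a design fault.
- **The headline claim of power for about a 50% reduction** concerns parasite prevalence and infection incidence, not this outcome. That also stands.

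A reader might infer more than the article supports. Applying the full 33% loss to the control sample would make the shortfall look larger, but that is a twelve-month figure that fits neither round. Two-sided power is lower still, but the plan specifies a one-tailed test, so it has no bearing on whether the stated figure follows from the stated inputs. Nor does this cast doubt on the survey and cohort calculations, which reproduce.

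**Conclusion.** The stated 80% is wrong as written. From the article's own inputs, power for RDT positivity at the stated effects is about 72% in both strata, so the type two error is about 28% rather than 20%. On the most lenient of the conventions tabulated it is about 76%. None of those variants of the stated inputs brings either stratum to 80%.

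The result rests on reading the 5% as a one-tailed type one error and on the c − 1 form, both supported by the reproduced survey and cohort figures. It uses the full enrolled control cohort, as at round one. The round-two figure of about 70% rests on linear loss, which the article does not state.

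**What to change.** In the subsection on RDT positivity during campaign rounds, do one of the following:

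- state about 72% power for the 33% reduction (30% to 20%) and the 50% reduction (10% to 5%); or
- keep 80% power and state detectable reductions of about 37% (30% to 19.0%) and 55% (10% to 4.5%), with the odds ratios changed to match; or
- if other inputs or another formula produced the 80%, state them.

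Add that the figures assume the full enrolled control cohort, as at round one, and that round-two power will be somewhat lower. Qualify the Discussion's general statement of 80% power within strata for this outcome.

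The cost is two restated figures and a sentence, slightly less favourable than the present text. Clusters, sample and conduct are unchanged.
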